### Statistical analysis

Analyses will be performed according to intention to treat. For the primary outcome, a linear mixed effects regression model will be fit with time in range from 16 weeks gestation until delivery as the dependent variable adjusting for baseline time in range, insulin delivery modality and clinical centre as a random effect. A point estimate, 95% confidence interval and *p*-value will be reported for the treatment effect based on the linear regression model.

For secondary glycaemic outcomes, similar models will be used. Linear regression models will compare continuous outcomes between treatment groups by adjusting for corresponding baseline metrics of insulin delivery modality, clinical centre as a random effect. Generalized linear mixed effects models will be used to compare CGM measured episodes of hypoglycaemia.

Selected CGM outcomes (mean CGM glucose, time in, above and below range, glucose SD and CV) will be calculated for the overnight period (23.00-07.00 h). These same selected CGM outcomes will also be calculated for each of the first, second and third trimesters separately, with similar linear models used to compare between group differences.

For assessing group difference in obstetric outcomes, infant outcomes and safety outcomes, linear regression models will be used to compare continuous and ordinal variables. Logistic regression will be used to compare categorical variables, and Poisson regression models will be used to compare event rates, while adjusting for baseline insulin delivery modality and random clinical centre effect. For analysis of adverse events, formal statistical comparisons will only be performed when there are enough observed events.

For assessing group difference in questionnaire data at 34-36 weeks, linear regression models will be fit while adjusting for corresponding baseline scores, insulin delivery and clinical centre.

For the postpartum data analysis, a linear mixed effects regression model will be fit with time in range from trial entry during pregnancy through until 24 weeks postpartum as the dependent variable. This model will adjust for baseline time in range and insulin delivery modality as fixed effects, and clinical centre and subject as random effects. We will also evaluate whether there is a difference in the therapeutic effect of closed-loop between pregnancy and postpartum. Predictive, generalised linear models will be used to explore correlations between maternal insulin doses, infant feeding and postpartum glycaemia.

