### Sample size estimation

The power calculations aim to compare the effect of closed-loop on the time spent in the target glucose range (3.5-7.8 mmol/L) and are based on data from our previous studies of CGM and closed-loop in type 1 diabetes pregnancy [6, 19, 20]. To detect a 10% difference the time spent in the CGM Time In Range (TIR) 3.5-7.8 mmol/L between closed-loop and standard insulin delivery, 98 participants are needed to achieve 90% power and an alpha level of 0.05 (two-tailed). The standard deviation of the primary efficacy outcome is 15% as observed in the CONCEPTT trial [6]. We anticipate 10% pregnancy losses and up to 10% of randomized participants who withdraw, which takes the total sample size to *n* = 124 (62 per arm) participants randomized.

The postpartum 6 month follow up is an exploratory add-on study within the trial, with the sample size determined by the number of eligible participants at the time of implementing the protocol amendment.

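### The Poisson model for event rates makes no stated allowance for variation between women, so intervals for the more frequent recurrent events may be too narrow (minor)

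*Protocol article*

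**What the plan says.** The Statistical analysis section of the protocol article assigns methods to the obstetric, infant and safety outcomes by type of variable. For counts it states: "Poisson regression models will be used to compare event rates, while adjusting for baseline insulin delivery modality and random clinical centre effect". It then adds a condition: "For analysis of adverse events, formal statistical comparisons will only be performed when there are enough observed events". No threshold for that condition is given.

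Two neighbouring statements limit the point. CGM hypoglycaemia has its own model: "Generalized linear mixed effects models will be used to compare CGM measured episodes of hypoglycaemia". The postpartum time-in-range model names "clinical centre and subject as random effects", so a participant-level term is written out there but not for event rates.

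The Poisson sentence does not list the outcomes it covers. The natural candidates are ketoacidosis, severe hypoglycaemia and adverse device effects (Safety outcomes, where both frequency and severity are asked for) and maternal hospital admissions (Obstetric outcomes). No expected rate or dispersion is given for any of them.

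**The concern.** A Poisson model sets the variance of each woman's count equal to its mean. The candidate outcomes can recur in the same woman, and women may differ in risk for reasons that baseline insulin modality and centre do not capture. The counts then vary more than the model allows. A random centre effect picks up differences between sites and leaves differences between women within a site untouched.

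Under that condition, model-based standard errors for the rate ratio are too small, and a difference in either direction is declared more often than the nominal 5%. Safety in terms of adverse event rates is among the protocol's Primary research questions, so a falsely precise rate ratio could be read as harm or as reassurance about a device used in pregnancy.

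**Working it through.** **The plan's own figure.** The only computed figure is the sample size for the primary outcome (difference 10 points, SD 15, two-sided alpha 0.05, power 90%). The normal formula gives 2 × (1.960 + 1.282)² × 15² / 10² = 47.3, so 48 per arm. The t-test version gives 48.26, so 49 per arm and 98 in total, as stated. Allowing for 20% loss, 98 / 0.8 = 122.5, so 123, or 124 with equal arms. The figure reproduces and does not depend on the event-rate model.

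**Inputs for the event-rate check.**
- From the protocol: 62 women per arm, 1:1 allocation, adjustment for insulin modality.
- Assumed: mean events per woman (mu), and the variance of a gamma frailty between women (theta).

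**Formulae.** With one count per woman:
- variance / mean: phi = 1 + mu × theta
- true SE / Poisson SE: √phi
- approximate true type I error: 2 × (1 − Φ(1.96 / √phi))

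For phi = 1.5, 2, 3 and 4, the SE ratio is 1.22, 1.41, 1.73 and 2.00, and the type I error is 11%, 17%, 26% and 33%. Which phi is plausible depends on the event rate. At mu = 0.1, phi = 2 needs theta = (2 − 1) / 0.1 = 10, and phi = 3 needs theta = 20.

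**Simulation.** The large-sample formula is unreliable for sparse counts, so it was checked by simulation with no true effect and 2,000 runs per cell. A Poisson model with arm and modality was fitted, with model-based and then robust standard errors.

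| mu | theta | SE ratio | Formula | Simulated, model-based SE | Simulated, robust SE |
|---|---|---|---|---|---|
| 0.05 | 1 / 2 / 5 | 1.02 / 1.05 / 1.12 | 5.6 / 6.2 / 8.0% | 0.4 / 0.7 / 1.3% | 0.4 / 0.7 / 0.6% |
| 0.1 | 1 / 2 / 5 | 1.05 / 1.10 / 1.22 | 6.2 / 7.4 / 11.0% | 3.4 / 4.5 / 6.2% | 3.0 / 3.5 / 4.2% |
| 0.3 | 1 / 2 / 5 | 1.14 / 1.26 / 1.58 | 8.6 / 12.1 / 21.5% | 9.0 / 11.0 / 21.1% | 5.7 / 5.3 / 6.6% |
| 1 | 1 / 2 / 5 | 1.41 / 1.73 / 2.45 | 16.6 / 25.8 / 42.4% | 15.5 / 24.1 / 41.0% | 5.9 / 5.7 / 6.8% |

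With theta = 0 the model-based error was 0.5% to 4.5% at these four rates, so the excess comes from the heterogeneity.

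**Limits of the check.** Monte Carlo error near 5% is about √(0.05 × 0.95 / 2000) = 0.5 points. Centre was left out, because it cannot absorb variation between women within a site. All 62 women per arm were given equal follow-up. Runs with no event in one arm were discarded: 190 to 273 of 2,000 at mu = 0.05, 7 to 30 at mu = 0.1, and none at the higher rates. Negative binomial regression was not simulated.

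**The case against.** The strongest reply is that this is detail for the analysis plan. A condensed article names a model family and leaves the variance estimator, the dispersion check and the offset to a document that is not shown here. Poisson regression with robust standard errors is still Poisson regression, so the printed sentence permits one of the remedies, and the word rates already implies follow-up time. This stands in part: nobody can say from the article that robust errors are excluded. But the article goes beyond naming a family. It fixes the covariate and the random effect, and the structure it fixes has no place for variation between women. The subject effect in the postpartum model is only modest support, since that model has repeated measurements on each woman.

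A second reply is rarity, and it stands for two outcomes. The Discussion groups severe hypoglycaemia and ketoacidosis among rarer outcomes, to be examined in a pooled analysis of individual patient data. At such rates the Poisson model does little harm. The rule on enough observed events does not settle the matter for the rest, however. It tends to drop the sparse comparisons and keep the frequent ones, where unmodelled heterogeneity matters most.

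A reader might infer more: that every event-rate interval will be too narrow, with error rates of 11% to 33% across the board. The documents do not support this. They give neither rates nor dispersion, and at low rates the simulated error is below nominal. Nor is centre the only adjustment, since insulin modality is also included. The Background remark on minimal variation between centres concerns glycaemic attainment and says nothing about event rates.

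**Conclusion.** The point holds in conditional form and is minor. The stated model makes no allowance for variation between women; if recurrent events cluster within women and model-based standard errors are used, the intervals will be too narrow. Under assumed frailty variances of 1 to 5, type I error is about 9% to 21% at 0.3 events per woman and 16% to 41% at 1 event per woman. At 0.1 or fewer events per woman with frailty variance up to 2, it is 0.4% to 4.5%.

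The practical reach is the commoner recurrent outcomes that would actually be tested, such as hospital admissions or adverse device effects, provided that they fall under this sentence. Severe hypoglycaemia and ketoacidosis are probably too rare to be affected. CGM-measured hypoglycaemia episodes have a separate model. The mechanism is certain; the size is not, because it rests wholly on assumed rates and heterogeneity.

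**What to change.** State that event rates will be compared by negative binomial regression, or by Poisson regression with participant-level robust standard errors, with log follow-up time as offset and the same covariates. The offset should be explicit because follow-up will differ between women: "We anticipate 10% pregnancy losses and up to 10% of randomized participants who withdraw". It would also help to name the outcomes that the model covers and to report the proportion of women with at least one event beside each rate. If the analysis plan already specifies robust errors, a cross-reference is enough.

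The cost is a sentence and a model option. Intervals will be somewhat wider where events cluster. The negative binomial model may fail to converge for sparse events, where robust Poisson can be used instead. Robust errors are not a perfect cure: in the simulations at 0.3 and 1 event per woman they brought type I error to between 5.3% and 6.8%.

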### Sample size estimation

The power calculations aim to compare the effect of closed-loop on the time spent in the target glucose range (3.5-7.8 mmol/L) and are based on data from our previous studies of CGM and closed-loop in type 1 diabetes pregnancy [6, 19, 20]. To detect a 10% difference the time spent in the CGM Time In Range (TIR) 3.5-7.8 mmol/L between closed-loop and standard insulin delivery, 98 participants are needed to achieve 90% power and an alpha level of 0.05 (two-tailed). The standard deviation of the primary efficacy outcome is 15% as observed in the CONCEPTT trial [6]. We anticipate 10% pregnancy losses and up to 10% of randomized participants who withdraw, which takes the total sample size to *n* = 124 (62 per arm) participants randomized.

The postpartum 6 month follow up is an exploratory add-on study within the trial, with the sample size determined by the number of eligible participants at the time of implementing the protocol amendment.

### Trial management

Norfolk and Norwich University Hospital NHS Foundation Trust (NNUH) is the trial sponsor and has delegated responsibility for the overall management of the trial to the chief investigator and Norwich Clinical Trials Unit, including the trial design, coordination, monitoring and analysis and reporting of results. A Trial Management Group TMG has been set up to assist with developing the design, co-ordination and strategic management of the trial.

### Data management

Data and statistical analyses will be handled by the Jaeb Center for Health Research, Tampa, Florida, United States of America in conjunction with Norwich Clinical Trials Unit, Norwich, United Kingdom.

### Trial steering committee

The Trial Steering Committee (TSC) is responsible for oversight of the trial in order to safeguard the interests of trial participants. The TSC will meet 6-monthly to review progress of the trial and provide advice to the chief investigator, Norwich Clinical Trials Unit, funder and sponsor.

### Independent data monitoring committee

The Independent Data Monitoring Committee (IDMC) is responsible for safeguarding the interests of trial participants, monitoring the accumulating data and making recommendations to the TSC on whether the trial should continue as planned. The IDMC is the only oversight body that has access to unblinded accumulating comparative data.

## Discussion

This trial aims to evaluate the clinical efficacy of automated closed-loop in pregnant women with type 1 diabetes. It will also provide insight into women’s and health care professionals’ experiences of using closed-loop as well as estimates of its cost-effectiveness and cost-utility which will inform provision of closed-loop in NHS healthcare settings. It may be able to assess whether closed-loop has an effect on obstetric and neonatal health outcomes.

Future individual patient data meta-analyses using data from AIDAPT and four ongoing studies of closed-loop (NCT0452097, NCT03774186, NCT04902378, NCT04492566) are planned to examine the effects on rarer pregnancy outcomes such as severe hypoglycaemia and diabetic ketoacidosis events. This may also be able to examine differences between different hybrid closed-loop systems, including commercially available systems and pregnancy-specific automated insulin delivery [10, 31].

Results from studies in non-pregnant populations suggest that automated insulin delivery systems can safely improve glycemia across age groups ranging from very young to older aged people with type 1 diabetes. Results from two short duration randomized crossover studies performed during pregnancy are conflicting, one with and one without improved time spent in the type 1 diabetes pregnancy target glucose range [19, 20]. This is the largest randomized study to examine use of closed-loop insulin delivery throughout pregnancy. It will inform patients, caregivers, healthcare professionals and funding agencies regarding the use of automated insulin delivery in pregnant populations with type 1 diabetes.

### Dissemination

A report will be written for the funding bodies and for peer-reviewed publication and will be disseminated to international lay and scientific audiences.

## Data Availability

Requests for access to trial data and stored samples will be considered, and approved in writing where appropriate, after formal application to the TSC. Inquiries for data should be addressed to the principal investigator [name].

## Abbreviations

CGM: Continuous glucose monitoring
CV: Coefficient of variation
EQ-5D: Euroqol Five Dimensions Health-Related Quality of Life Questionnaire
HbA1c: Haemoglobin A1c
IDMC: Independent data monitoring committee
INSPIRE: the INsulin delivery Systems: Perspectives, Ideas, Reflections and Expectations questionnaire
MDI: Multiple daily injections
NICE: National Institute for Health and Care Excellence
PPI: Patient and public involvement
SAEs: Serious Adverse Events
SADEs: Serious Adverse Device Effects
SD: Standard deviation
TSC: Trial steering committee
TIR: Time in range
